## 1. Summary of the research study

|                           |                                                                                                                                                                                                                                                                                                                                                                                                                                                                                                                                                                                                                                                                                                                                                                                                                                                                                                                                                                                                                                                                                                                                                                                                                                                                                                                                             |
|---------------------------|---------------------------------------------------------------------------------------------------------------------------------------------------------------------------------------------------------------------------------------------------------------------------------------------------------------------------------------------------------------------------------------------------------------------------------------------------------------------------------------------------------------------------------------------------------------------------------------------------------------------------------------------------------------------------------------------------------------------------------------------------------------------------------------------------------------------------------------------------------------------------------------------------------------------------------------------------------------------------------------------------------------------------------------------------------------------------------------------------------------------------------------------------------------------------------------------------------------------------------------------------------------------------------------------------------------------------------------------|
| Sponsor                   | French public funding agency Délégation à la Recherche Clinique et à l'Innovation (DRCI), Versailles, France                                                                                                                                                                                                                                                                                                                                                                                                                                                                                                                                                                                                                                                                                                                                                                                                                                                                                                                                                                                                                                                                                                                                                                                                                         |

| Title                     | Evaluation of the analgesic effect of music in critically ill patients during potentially painful nursing procedures: a pilot study (Painkiller)                                                                                                                                                                                                                                                                                                                                                                                                                                                                                                                                                                                                                                                                                                                                                                                                                                                                                                                                                                                                                                                                                                                                                                                            |
| Justification/
Context | Among critically ill patients who are able to communicate, nearly 60% report pain during their intensive care unit (ICU) stay. Pain's causes are numerous and essentially related to the care management and invasive procedures (catheters, drains removal, post-operative care, patient mobilization during bed bathing and nursing care procedures, wound care, tracheal suctioning...). Pain management relies on a simple strategy that associates: prevention, assessment, pharmacological and nonpharmacological pain treatment. However, whereas pain control in intensive care unit relies mainly on pharmacotherapy, non-pharmacological interventions such as music have been evaluated in various other settings such as pediatrics, oncology, neurology and psychiatry. In these patients, a recent Cochrane group metaanalysis concludes to a reduction in pain intensity and analgesic requirements. In critically ill patients undergoing mechanical ventilation, music effects have been evaluated in another Cochrane metaanalysis of studies demonstrating a decrease of anxiety occurrence, heart rate, respiratory rate but also blood pressure. Thus, it appears interesting to assess the therapeutic value of music as a nursing intervention in potentially painful nursing procedures in the intensive care unit. |
| Objectives                | Primary: To evaluate the length of pain exposure for critically ill patients unable to communicate undergoing mechanical ventilation, whether or not receiving music, during nursing care.
Secondary: To evaluate the occurrence of peak pain exposure for critically ill patient unable to communicate undergoing mechanical ventilation, whether or not receiving music, during nursing care.                                                                                                                                                                                                                                                                                                                                                                                                                                                                                                                                                                                                                                                                                                                                                                                                                                                                                                                            |
| Study design              | Prospective, interventional, comparative single center study                                                                                                                                                                                                                                                                                                                                                                                                                                                                                                                                                                                                                                                                                                                                                                                                                                                                                                                                                                                                                                                                                                                                                                                                                                                                                |
| Inclusion criteria        | Adults patients older than 18 years of age, admitted in intensive care unit, receiving invasive mechanical ventilation, and with a Richmond Agitation Sedative Scale (RASS) score between -3 and +4                                                                                                                                                                                                                                                                                                                                                                                                                                                                                                                                                                                                                                                                                                                                                                                                                                                                                                                                                                                                                                                                                                                                         |
| Exclusion criteria        | Patients receiving neuromuscular blocking agents or patients with a RASS score <-3                                                                                                                                                                                                                                                                                                                                                                                                                                                                                                                                                                                                                                                                                                                                                                                                                                                                                                                                                                                                                                                                                                                                                                                                                                                          |
| Outcomes                  | Primary: Proportion of pain exposure during nursing procedures.
Total length of pain exposure (minutes) to a BPS score over or equal to 5 divided by total length of nursing procedure
Secondary: Proportion of maximal pain exposure during nursing procedures Total length of exposure to the maximal BPS score (over or equal to 5) among total length of nursing procedure                                                                                                                                                                                                                                                                                                                                                                                                                                                                                                                                                                                                                                                                                                                                                                                                                                                                                                                                          |
| Sample size               | Pilot study, whose purpose is to obtain preliminary data and for which it is not possible to calculate a study sample size. The number of patients to be included was fixed at 60, ie 30 patients in each group (morning bed bathing and wound care with and without music).                                                                                                                                                                                                                                                                                                                                                                                                                                                                                                                                                                                                                                                                                                                                                                                                                                                                                                                                                                                                                                                                |
| Intervention              | Eligible patients will be consecutively included. The first 30 patients will be included in the control group and the next 30 patients in the intervention group. In the intervention group, patients will be exposed to music during the morning bed bath, using headphones connected to an MP3 converter via a Bluetooth connection. The same selection of passages by Mozart will be used in all patients. The music will start at the same time as the bed bath and continued throughout the bath and for 30 minutes after the end of the bath. Sound intensity will do not exceed 60 decibels. In both groups, BPS scores will be determined by a nurse, who will not be involved in providing the bath. The BPS score will be determined just before the bath; at completion of the bath; and 30, 60, and 120minutes after the end of the bath. During the bath, the BPS score will be assessed in cases of variations of BPS score $\geq 5$ . Total length of the bath will be recorded.                                                                                                                                                                                                                                                                                                                                             |
| Statistical analysis      | Quantitative parameters will be described as median (interquartile range [IQR]) and qualitative parameters as number (%). All tests will be two-tailed at the 0.05 significance level with a two-sided hypothesis.                                                                                                                                                                                                                                                                                                                                                                                                                                                                                                                                                                                                                                                                                                                                                                                                                                                                                                                                                                                                                                                                                                                          |

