### **4.3 Eligibility criteria**

#### **4.3.1 Inclusion criteria**

- adults patients admitted in intensive care unit if they were older than 18 years of age
- receiving invasive mechanical ventilation,
- with a Richmond Agitation Sedative Scale (RASS) score between -3 and +4.

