### **5. Intervention**

#### **5.1 Modalities of enrolment**

In this study, eligible patients will be consecutively included. The first 30 patients will be included in the control group and the next 30 patients in the intervention group.

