#### **6. Data collection**

Demographic and clinical data will be collected prospectively at the bedside on a standardized form. Demographics data: age, gender, reason for ICU admission (medical, emergency surgery, scheduled surgery), comorbidities, reason for mechanical ventilation, ICU length of stay before inclusion. Patients characteristics at inclusion: presence of tracheotomy, chest tubes, central venous catheter, arterial line, gastric tube, surgical drain tube. Nursing care characteristics will be assessed in both groups at baseline; during; and 30, 60, and 120 minutes after the end of the evaluated nursing care. Total length of nursing procedure will be recorded. Data related to pain assessment: Total length of pain exposure (minutes) to a BPS score over or equal to 5; and total length of exposure to the maximal BPS score (over or equal to 5).

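### With no limit on prior stay at entry and the first 30 patients all controls, patients already eligible when the study opens enter almost only as controls, which may load that group with longer-stay patients

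*Protocol*

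**What the plan says.** Protocol section 4.3.1 lists three entry conditions: "adults patients admitted in intensive care unit if they were older than 18 years of age", "receiving invasive mechanical ventilation" and "with a Richmond Agitation Sedative Scale (RASS) score between -3 and +4". The summary repeats them, admitting "Adults patients older than 18 years of age, admitted in intensive care unit, receiving invasive mechanical ventilation" with the same RASS range. The exclusions in the summary are "Patients receiving neuromuscular blocking agents or patients with a RASS score <-3", and section 4.3.2 matches. None of these refers to time since ICU admission, since intubation, or since the first bath at which the patient could have been scored.

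Section 5.1 states: "In this study, eligible patients will be consecutively included". Allocation follows order of entry: "The first 30 patients will be included in the control group and the next 30 patients in the intervention group".

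Section 7 requires written consent from a relative or surrogate before inclusion. Section 6 collects "ICU length of stay before inclusion" as a baseline item. Section 8 names Fisher's exact test and the t, Mann-Whitney or Wilcoxon test.

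**The concern.** On opening day the eligible patients are a cross-section of the unit. A cross-section over-represents long stays, because a patient ventilated for three weeks is far more likely to be present on a given day than one ventilated for two days. After opening, patients enter mostly as they newly become eligible. Because the first 30 places are all control places, the opening cross-section falls almost wholly in one group.

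This differs from the usual objection to a before-and-after comparison, which concerns change over time in patients, staff or practice. Here the groups differ even in a unit where nothing changes, because the entry rule draws them from different populations.

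Controls may therefore have been ventilated longer before the scored bath. If pain behaviour during care varies with stage of illness, a difference between groups in the share of bath time at BPS 5 or more would partly reflect that stage and not the music.

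**Working it through.** **No figure to reproduce.** Section 4.2 fixes 60 patients (30 per group) without a calculation, and the protocol gives no unit census, ventilation time or consent rate. All inputs below except the 30 per group are assumptions.

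**Step 1: time already elapsed in patients present at opening.** For a unit in steady state, mean elapsed time = (mean / 2) × (1 + CV²).
- Mean 5 days, CV 1: 2.5 × 2 = 5.0 days
- Mean 7 days, CV 1: 3.5 × 2 = 7.0 days
- Mean 10 days, CV 1.5: 5 × 3.25 = 16.25 days

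**Step 2: effect on the control mean.** Let m controls be patients present at opening, and let new patients enter at about day 1. Control mean = [m × elapsed + (30 − m) × 1] / 30, against about 1 day with music. With mean 7 days and CV 1:

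| m | Share of controls | Control mean (days) |
|---|---|---|
| 3 | 10% | (21 + 27)/30 = 1.6 |
| 5 | 17% | (35 + 25)/30 = 2.0 |
| 10 | 33% | (70 + 20)/30 = 3.0 |
| 15 | 50% | (105 + 15)/30 = 4.0 |

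Over means of 5 to 10 days and CV 1 to 1.5, the control mean is 1.7 to 3.5 days at m = 5 and 2.3 to 6.1 days at m = 10.

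**Step 3: how large m could be.** A simulation used Poisson arrivals in steady state, 6 to 15 ventilated patients, lognormal ventilation time (mean 7 or 10 days, log SD 0.9), and a mean of 1.5 days to eligibility. Inclusion was each morning, the first 30 as controls. The time measured runs from the start of ventilation, so it stands in for ICU stay and is not identical to it.
- *Everyone consents at once:* about 4 to 15 of 30 controls were already ventilated at opening, against 0 with music. The low end arises when only one patient a morning can be scored (4.0 to 7.7). The standardised difference in log prior ventilated time was 0.25 to 0.78.
- *60% consent with a mean 2-day delay:* 2.4 to 7 of 30 controls, still about 0 with music. The standardised difference was 0.11 to 0.37.

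**Step 4: effect on the primary outcome.** Bias = (m / 30) × D, where D is the difference in share of bath time at BPS 5 or more between patients present at opening and new patients. The documents give no value or sign for D. If D = 0 there is no bias. If D were 20 percentage points, purely for illustration:
- m = 2: 2/30 × 20 = 1.3 points
- m = 6: 6/30 × 20 = 4 points
- m = 15: 15/30 × 20 = 10 points

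A positive D would flatter music; a negative D would count against it by the same amount.

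**Step 5: the remedy.** Excluding only patients who had passed an eligible morning bath before opening brought the standardised difference to about -0.08 to 0.03 in most settings. The worst case was -0.22, in a large unit scoring one patient a morning, where a queue builds up and later entrants wait longer. Recruitment lengthened by about 1 to 9 days.

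**The case against.** **The root cause is allocation.** Under concurrent randomisation the same criteria would create no systematic imbalance, and broad criteria are not an error in themselves. This stands. The missing limit matters only in combination with section 5.1. It still deserves its own correction, because it can be removed while the sequential design is kept.

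**Absolute wording would be wrong.** A reader might infer that every patient ventilated at opening becomes a control, that none can receive music, and that long-stay patients fill the control group. The documents do not support this. Section 7 requires surrogate consent first, so some eligible patients will never enter. A patient ventilated at opening but too deeply sedated, or whose surrogate signs late, could in principle reach the music group, though this was rare in the simulations (at most a 1.5% chance of any such patient in a setting). In nearly every setting, patients present at opening are a minority of the 30 controls.

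**The link to pain is assumed.** Nothing in the protocol ties prior stay to BPS during care. This stands: an imbalance in prior stay follows from the rules, but a bias in the primary outcome is only possible.

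**Prior stay is recorded and could be adjusted for.** Section 6 makes the imbalance visible. Section 8 names only two-group tests, but covariate adjustment is commonly left to a statistical analysis plan, which may exist, so its absence here is not counted as a fault. Adjustment after the fact is weaker than an entry rule that avoids the imbalance, especially with 30 per group.

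**Conclusion.** The point holds in a limited form. The entry rules and the order of allocation together send patients already eligible at opening almost entirely to the control group. The expected direction is longer prior ventilation in controls, with no time trend needed.

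The size is uncertain. It rests on assumed census, ventilation time, sedation pattern and consent, and the log SD of 0.9, which drives the weighting to long stays, was not varied in the simulations. Under those assumptions about 2 to 15 of 30 controls are affected and the standardised log difference is about 0.1 to 0.8. The lower part of that range is more plausible once consent is allowed for.

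It would be tempting to conclude that the comparison is biased in favour of music. The documents do not show this, because the size and sign of any difference in pain share are unknown. For a pilot, this is an avoidable baseline difference worth removing, not a reason to discard the design.

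**What to change.** Add one sentence to section 4.3.1 and to the summary: *patients who had already met all criteria at a morning bath before the study opened are not eligible.* State also that patients who first become eligible after opening may enter at a later bath once surrogate consent is signed, under the same rule in both groups. The sentence concerns eligibility only, so it also covers patients scored during a surgical dressing, which section 5.2 allows.

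Report ICU length of stay before inclusion by group, and add a supportive comparison of the primary outcome adjusted for it. Both use data already collected under section 6, and both remain possible if enrolment has begun.

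The cost is one amendment and about 1 to 9 more days of recruitment under the assumptions above, with the same 60 patients.

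A stricter rule, admitting patients only at their first eligible bath, is not recommended. With 60% consent and a mean 2-day delay it loses anyone whose surrogate has not yet signed that morning. It lengthened recruitment from 62 to 109 days in one setting (15 ventilated patients, mean 7 days), and several-fold in other runs. It would also favour patients whose relatives are quickly available.

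The recommended change does not remove time-trend bias from sequential allocation, and a small reverse imbalance can remain if only one patient a morning can be scored.
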